## Assignment of interventions: allocation

### Sequence generation {16a}

Block randomization will be by cluster using the program calculator.net. Each clinical site is a cluster, and there will be a 5:1 ratio in the assignment of *both* LACDHS and LACDMH clinics assigned to the intervention arm (offering STUDS) as compared with the TAU arm. A total of 18 study sites will be randomized on a 5:1 intervention to TAU ratio basis, with three TAU sites and fifteen intervention sites split as follows: 11 primary care clinics (9 intervention, 2 TAU) and 7 mental health clinics (6 interventions, 1 TAU).

### Concealment mechanism {16b}

There is no concealment.

### Implementation {16c}

Statistician [name], will perform the randomization at a clinic level using a computer program. The study is a cluster-randomized design protocol. Individual clinics will be assigned to the intervention and TAU on a 5:1 ratio. Study participants empanelled or otherwise being treated by clinicians at TAU clinics are therefore considered to be in the TAU arm, and study participants who receive care from intervention sites are in the intervention arm. Clinic staff and study coordinators will notify clinics of their assignments. Following the eligibility check and informed consent, the research team will enroll participants into either clinics that provide smoking cessation services or TAU clinics. The sites will be identified by a rotating code, so participants cannot learn which sites are TAU.

## Assignment of interventions: blinding

### Who will be blinded {17a}

There is no blinding.

### Procedure for unblinding if needed {17b}

There is no need for unblinding.

## Data collection and management

### Plans for assessment and collection of outcomes {18a}

Data will be collected in-person by research interviewers at the participant’s primary care clinic or site associated with where they usually obtain county-provided services. Research interviewers will complete brief medical and mental health assessments, including smoking status. Study measures will be administered on a tablet computer and captured in real time using Qualtrics, a secure, direct data entry method HIPAA-compliant Web-based survey platform. Each data collection point will take approximately 30–45 min. The following interviews and self-report measures will be administered during the baseline, 3-month, 6-month, and 12-month in-person visits: (1) Beck Anxiety Inventory (BAI), a self-report assessment to measure anxiety symptomatology [13]; (2) Beck Depression Inventory, Revised (BDI-II), a widely used measure in psychological research and clinical practice of depressive symptomology [14]; (3) Fagerstrom Test for Nicotine Dependence (FTND), a widely used study measure of nicotine dependence [15]; (4) Minnesota Nicotine Withdrawal Scale (MNWS) to measure symptoms of craving for tobacco, irritability, anxiety, difficulty concentrating, and restlessness after smoking cessation [16]; (5) Wisconsin Predicting Patient’s Relapse WI-Prepare, a scale that predicts smoking cessation outcomes [17]; (6) 30-day Timeline Followback Assessment (TLFB) measures quantity and frequency of smoking [18]; (7) Daily Smoking Log to assess smoking frequency in the 7 days prior to group meeting; (8) Questionnaire of Smoking Urges-Brief (QSU-Brief) designed to measure research participants’ level of craving and urges to smoke cigarettes assessment [19]; (9) Patient Satisfaction Questionnaire Short Form (PSQ-18) assessing satisfaction with medical care [20]; (10) World Health Organization Quality of Life-Brief (WHOQOL-BREF), a self-report assessment to measure the quality of life, with subscales, which has been extensively validated in studies worldwide ; and (11) The Quit Smoking Measure will consider study participants to have “quit” smoking cigarettes during the study if they self-report smoking no cigarettes within the last 7 days. We initially planned that this would be corroborated by exhaled carbon monoxide level of <5 ppm (parts per million). CO breathalyzer (piCO+Smokerlyzer) test and rapid dipstick cotinine test (NicCheck) were administered at each in-person study visit, but breathalyzer and urine testing were temporarily discontinued in March 2020 due to the pandemic. See Table 1 for procedures and measures administered at each study visit.

**Table 1 Tab1:** Procedures and measures administered at each study visit

Month	0	3	6	12
Study visit	1	2	3	4
Informed consent	X			
Medical assessments	X	X	X	X
Behavioral Measures Battery	X	X	X	X
Weekly Cigarette Log	X	X	X	X
Patient Satisfaction Questionnaire Short Form (PSQ-18)	X	X	X	X

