At the first interview, the researcher will explain the study and answer any questions participants may have. If they agree to participate in the study, they will be enrolled into the study at the first interview. The researcher will then set up a schedule to meet again at 3 months, 6 months, and 12 months. To enhance retention, participants will be asked to provide contact information for the research team to keep in contact for subsequent follow-up interventions.

At each interview, the researcher will complete brief medical and mental health assessments which will ask about participants’ overall physical and mental health, including their smoking status. Data will be collected in-person by the research team via computer-assisted interviews which will include self-reports on smoking history, anxiety, stress, quality of life, and participant satisfaction. Initially, at each interview, we planned on asking participants to complete the carbon monoxide (CO) breathalyzer test and provide a urine sample for the rapid dipstick cotinine test to determine the use of cigarettes and levels of nicotine in the body. The urine collected for this study was to be only tested for cotinine and no other substances. Breathalyzer and urine testing were temporarily suspended in March 2020 in response to the COVID-19 pandemic when enrollment and follow-up assessments shifted from in-person to telephone and in-person visits are not anticipated to resume. Prior to suspension, 12 participants in the TAU arm and 69 participants in the intervention arm completed CO and urine testing.

Participants who are assigned to clinics that provide smoking cessation services will also be asked about the frequency of their participation in the smoking cessation services during the 12-month period. Interviews will be conducted at the participating LAC outpatient clinic where participants receive their primary health care. The smoking cessation services will include a (1) weekly 60–75-min cognitive-behavioral therapy (CBT) smoking cessation counseling group which will be led by facilitators that have been trained through the Kick Ash program and may be a nurse, pharmacist, clinician, substance use disorder (SUD) counselor, behavioral health clinician, or counselor; and (2) smoking cessation medication that will be prescribed by a licensed, prescribing clinician. Smoking cessation medications will include varenicline (Chantix), bupropion (Zyban), and nicotine patches, gum, and lozenges.

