### Eligibility criteria {10}

Inclusion criteria for participants are as follows: (1) be 18 years old or older, (2) smoke three or more cigarettes or cigars per day, (3) have thought about stopping smoking, and (4) be enrolled in care at either LACDHS and/or LACDMH. Participants who use only electronic cigarettes, hookah, or other types of tobacco/nicotine will not be allowed in the study if they do not meet all inclusion criteria. Cigarette and cigar smokers who also use electronic cigarettes, hookah, or other types of tobacco/nicotine will be allowed in the study.

Exclusion criteria for participants are as follows: (1) under 18 years, (2) smoke less than three cigarettes or cigars per day, (3) not interested in stopping cigarette smoking, and (4) not enrolled in care at either LACDHS and/or LACDMH.

Based on our preliminary data and analysis, a significant number of dropouts are anticipated. An estimated 50% of enrolled participants will drop out. Since this is a pragmatic real-world trial, we accept the risk of a significant dropout rate. Furthermore, given that this is an implementation trial, study participants can continue to participate in the research assessments even if they do not participate in clinical services. A patient is considered a dropout if they report no longer wanting to participate in the research assessments or cannot be reached to complete research assessments.

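### Cigar smokers are eligible but the quit definition counts only cigarettes, so a cigar-only smoker scores as quit at every visit and a switch to cigars scores as success

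*Protocol article*

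**What the plan says.** **Who enters.** Under Eligibility criteria {10}, a participant must "smoke three or more cigarettes or cigars per day". The matching exclusion bars those who "smoke less than three cigarettes or cigars per day". The section adds: "Cigarette and cigar smokers who also use electronic cigarettes, hookah, or other types of tobacco/nicotine will be allowed in the study". Nothing requires cigarette smoking at entry.

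**What counts as quitting.** Under Plans for assessment and collection of outcomes {18a}, the Quit Smoking Measure scores a participant as having quit "if they self-report smoking no cigarettes within the last 7 days". The Discussion likewise describes seven days' abstinence from cigarettes. No section extends the criterion to cigars or treats cigar-only smokers separately.

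**What corroborates it.** Section {18a} says that an exhaled carbon monoxide level below 5 ppm was initially planned as confirmation. Trial design {8} reports that breath and urine testing was suspended in March 2020 and that "in-person visits are not anticipated to resume". It also gives the extent of testing up to then: "Prior to suspension, 12 participants in the TAU arm and 69 participants in the intervention arm completed CO and urine testing".

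**Where it is used.** Outcomes {12} makes the smoking cessation rate, intervention against treatment as usual (TAU), the primary outcome. Section {20c} carries the last value forward, so a participant seen once keeps the baseline smoking status.

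**The concern.** The eligibility rule and the endpoint cover different products. Someone who smokes only cigars can satisfy the entry rule and the quit rule on the same day. Such a participant adds a success to whichever arm the clinic is in, whatever the treatment does.

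Two other groups are affected after entry: cigarette smokers who move to cigars, and smokers of both who drop only the cigarettes. They are scored as abstinent while still smoking a product that would qualify them for the trial.

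The carbon monoxide check might have caught some of these cases, but it is no longer in use. The missing-data rule does not help either. Section {20c} describes it as tending to be conservative, but a cigar-only smoker lost after baseline is carried forward as quit. The article expects 50% dropout.

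At stake is the meaning of the primary outcome. Equal shares in the two arms dilute the contrast. Unequal shares bias it, and with three TAU clinics (Sequence generation {16a}) the arms could differ in cigar use by chance.

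**Working it through.** **Inputs from the article (Sample size {14}).** Abstinence 25% intervention v 5% TAU; 1000 participants in 14 sites v 200 in 3; 50% dropout; intra-cluster correlation 0.05; two-sided 5%; stated power 99.4%.

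**Assumed input.** c, the share of cigar-only smokers. The article gives no figure, so a range is shown.

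**1. The plan's own figure.** Use a design effect of 1 + (m − 1) × 0.05 in each arm and a two-proportion normal approximation with unpooled variance.
- Intervention after dropout: 500/14 = 35.7 per site, design effect 2.74, effective n 182.8.
- TAU after dropout: 100/3 = 33.3 per site, design effect 2.62, effective n 38.2.
- Standard error = √(0.25 × 0.75/182.8 + 0.05 × 0.95/38.2) = 0.0476. Then 0.20/0.0476 − 1.96 = 2.24, so power is 98.7%.
- Without dropout the same formula gives 99.6%.

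The stated 99.4% lies between these two. A pooled variance gives 88.3% with dropout and 94.8% without, so the stated figure fits only the unpooled form. The point made here does not depend on it.

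**2. Equal share in both arms.** If every cigar-only smoker is scored as quit and p is the true abstinence rate, the observed rate is c + (1 − c)p. For c = 5%: 0.05 + 0.95 × 0.25 = 28.75%, and 0.05 + 0.95 × 0.05 = 9.75%.

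| c | Intervention | TAU | Difference | Ratio | Power (unpooled, 50% dropout) |
|---|---|---|---|---|---|
| 0 | 25.0% | 5.0% | 20.0 points | 5.0 | 98.7% |
| 2% | 26.5% | 6.9% | 19.6 points | 3.8 | 96.3% |
| 5% | 28.75% | 9.75% | 19.0 points | 2.9 | 90.1% |
| 10% | 32.5% | 14.5% | 18.0 points | 2.2 | 77.0% |

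The difference shrinks by the factor (1 − c). Power falls faster because both proportions move up and their variances grow.

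**3. Share in one arm only.** That arm's rate is inflated by c(1 − p).
- c = 5%: 0.05 × 0.75 = 3.75 points if in the intervention arm; 0.05 × 0.95 = 4.75 points if in TAU.
- c = 10%: 7.5 and 9.5 points respectively.
- No true effect, 5% abstinence in both arms, c = 5% in one arm and 0 in the other: 9.75% v 5%, a spurious 4.75 points in either direction.

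**4. Switchers and dual users.** The article gives nothing to size this group. They are classified after treatment starts, so their share may differ between arms because of treatment as well as by chance.

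**The case against.** The case on the other side has five parts.

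- **Other readings of the definition.** Section {18a} speaks of quitting cigarettes during the study, and section {12} compares each time point with baseline. On that reading, someone who never smoked cigarettes cannot have quit them. This is possible, but no section makes cigarette use at baseline a condition of the measure, and the reading does nothing for those who switch to cigars.
- **Cigar-only smokers may not enter.** One exclusion removes people "not interested in stopping cigarette smoking". It may catch some of them, or the authors may use cigarette loosely for any smoking. It does not clearly bar them, because the quantity rules for both inclusion and exclusion name cigars.
- **Not every cigar smoker is affected at every visit.** A reader might infer that any cigar smoker is automatically quit. That does not follow. Someone who also smokes cigarettes must stop them for 7 days; only the cigar-only smoker is quit throughout.
- **Other smoking data exist.** A reader might infer that no other abstinence information remains. Section {18a} also lists a 30-day Timeline Followback (TLFB) and a daily smoking log. Neither is named as the quit criterion, and Table 1 calls its log a cigarette log, so product detail is uncertain. They may still allow a repair.
- **The effect may be small.** This stands. At 2% to 5% the difference moves by at most one point, and equal shares pull towards no effect. The steep fall in the ratio owes much to the small 5% TAU rate. A 10% share in one arm and none in the other is an extreme case.

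The exact interview wording is not shown. The finding therefore concerns the definition as the article states it.

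**Conclusion.** The mismatch is real and touches the primary outcome: the stated rule classifies some eligible, continuing smokers as abstinent. This is more than a detail left to another document, because the article states both the eligibility rule and the quit rule and they do not fit together.

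The size is unknown. With equal cigar-only shares of 2% to 10%, the 20-point planned difference would be observed as 19.6 to 18 points. An unequal share would bias the difference by c(1 − p) in the arm that has it. These figures assume that cigar-only smokers smoke no cigarettes at any visit, that all are scored as quit, and that under a corrected definition they would stop at the planned 25% and 5%.

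The article does not show that the trial's result will be materially wrong, or that the error favours the intervention. Nor does the contradiction reach hookah or e-cigarettes. Those products do not qualify anyone for entry, so whether abstinence should cover them is a separate choice.

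**What to change.** Define quit as no cigarettes and no cigars in the last 7 days, in the same words in both arms, and state that this is the primary endpoint definition.

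For visits already completed, derive it from the TLFB or the smoking log where the product was recorded. Where it was not, add a sensitivity analysis that excludes participants who smoked only cigars at baseline. That analysis removes the people who are quit by definition; it does not correct for those who moved to cigars later, and the report should say so.

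The cost is small: one definition and, where the interview asks only about cigarettes, one item. Some completed visits may lack product detail. Recruitment began in October 2019, the trial is unblinded, and section {21b} plans an interim look at the number who have stopped smoking. The redefinition should therefore be dated and fixed before outcome data are compared by arm.

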### Plans to promote participant retention and complete follow-up {18b}

To promote participant retention and respect the participants’ time during the study, participants will be compensated up to $50. Participants will receive a $10 gift card for the baseline, 3-month, and 6-month interview. At the final interview (12-month), participants will receive a $20 gift card. Compensation will be in the form of gift cards to a local store and will be made at the end of each of the four interviews. Additionally, all interviews will take place at the participant’s primary care clinic, or the site associated with where they usually obtain county-provided services, curbing possible inconveniences or transportation barriers to each study visit. To minimize missing data for those elements manually transcribed into Qualtrics, we will use that application’s data type restrictions to help enforce entry of required data elements.

### Data management {19}

The research team will store all study-related data in an electronic data capture (EDC) eCRF system (Qualtrics). Qualtrics is a secure, direct data entry method that is HIPAA compliant. This system is password protected and only accessible to the research team. Physician data includes paper source documents. The research team will provide pencil-and-paper individual surveys to physicians (*Clinical Staff Questionnaire – Clinical Survey*). Other selected clinic care team staff will be asked to complete the paper-and-pencil survey by their clinic administrator. The paper source documents will also be available online using the eCRF system, Qualtrics. Data will be transcribed from source documentation directly into a statistical program such as Statistical Analysis System (SAS). Clinic data will consist of data from the Online Real-time Centralized Health Information Database (ORCHID) at LACDHS and the Integrated Behavioral Health Information System (IBHIS) at LACDMH about relevant care processes at the participating clinics, both those randomized to offer the group session and those randomized to not offer the group session. Such data will be aggregated at the clinic level and provided to the research team by LACDHS/DMH staff based on the availability and capacity of LACDHS/DMH. Regulatory bodies such as the funding agency and/or Los Angeles County Department of Public Health Committee for the Protection of Human Subjects may have access to study data for the purpose of an audit to protect the rights and welfare of participants. Auditors are trained in the rules of confidentiality and will take the utmost care to keep study data confidential.

Identification numbers will be used to store the collected data, such as assessments. All study-related data will be stored in a secure, Web-based data capture system. The system will be password protected and only accessible to the research team. A cross-index of identifiable information will only be accessible to the research team to link participants to the identification numbers. Participants’ contact information and any other documents that contain names or any identifying information collected on paper will be scanned and saved to a HIPAA-compliant document storage system on ORCHID or IBHIS in accordance with the participants’ primary care clinic. The documents will then be confidentially destroyed. Files which contain any type of identifying information will be confidentially destroyed 5 years after the end of the study.

### Confidentiality {27}

Any information that is obtained in connection with this study that can identify participants will remain strictly confidential. The research team is trained in the rules of confidentiality as required by law and it is the research team’s responsibility to ensure that participant confidentiality is protected at all times. However, if the research team is required by law to disclose confidential information to the appropriate authorities to protect participant’s well-being and/or the well-being of others, the team will do so without participant’s consent. Additionally, study data or information that is published and discussed in conferences or in presentations will not include anything that could reveal participants’ identity.

To protect confidentiality during the smoking cessation counseling group, the facilitator leading the group will stress the importance of confidentiality among group attendees, emphasizing that attendees should not mention anything said in the group to anyone outside of the group. Additionally, the participants will share information during the counseling group at their own discretion. Clinic staff or participants’ LACDHS/LACDMH healthcare provider may eventually know that they are participating in the study. However, they do not have access to nor will be given any information the participants provide to us as part of the study.

Authorized representatives from the funding agency and/or from the Los Angeles County Department of Public Health Committee for the Protection of Human Subjects may ask to access the study data for the purposes of an audit. Auditors are trained in the rules of confidentiality and will take the utmost care to keep study data confidential.

### Plans for collection, laboratory evaluation, and storage of biological specimens for genetic or molecular analysis in this trial/future use {33}

Not applicable as we will not be collecting or storing biological specimens.

## Statistical methods

### Statistical methods for primary and secondary outcomes {20a}

Final analyses will begin in year 4 at quarters 2 and 3. Data analysis will utilize an intention-to-treat (ITT) approach as the primary analysis. An additional set of analyses will use a per-protocol (PP) paradigm that will only use subjects who attend at least 3, out of four visits, including month 12. Descriptive statistics will include number, percent, and mode for categorical data (gender, race/ethnicity, site, LACDHS/LACDMH, number of visits). Continuous variables of clinical characteristics (number of cigarettes smoked, number of years smoked, Fagerstrom score) and Behavioral Measures Battery will be used to describe the study population. Non-normal distribution will be transformed to satisfy the normality assumption for the parametric statistical tests. Scale variables will be presented as min, max, and median. Graphical presentations (histograms, boxplots, and spaghetti plots) will be used to facilitate the visualization of data and the time trend of endpoints and baseline variables. All statistical analyses will be performed using SAS 9.2 and a *P*-value <0.05 will be considered statistically significant.

For model 1, we will perform an analysis of covariance with the baseline value (site, racial-ethnic group, number of visits, age, weight, smoking status, and survey scores) as the covariate and compare the value at the end of the study. To evaluate the change over time between the groups that incorporates all the measures collected over the timeframe of the study, then a two-way repeated measures analysis of variance model will be used. For model 2, a multiple logistic regression model would be built using independent variables such as treatment group and pre-determined baseline covariates (including study site). We posit that using a covariate-adjusted model to evaluate outcome provides a sensitivity analysis for the primary results of a simple comparison of the achievement of smoking cessation. For both models, the analyses will incorporate the cluster-randomized design into the model using an appropriately chosen variance-covariance structure (up to the use of an unspecified structure). In addition, the models will include a term for LACDHS versus LACDMH sites and their interaction with the intervention group.

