### Methods in analysis to handle protocol non-adherence and any statistical methods to handle missing data {20c}

The primary analysis will use the intent-to-treat approach (ITT) which requires all randomized participants to be included in the statistical analysis and use the last value carried forward method to account for missing data, which tends to be conservative. Thus, if a patient only comes once, their smoking status and other characteristics will be that of baseline measurement and no change in the values with time will be noted.

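### Both covariate-adjusted models list clinic site as a covariate although clinics are randomised, and model 1 treats attendance as a baseline value

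*Protocol article*

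**What the plan says.** All places are in the protocol article.

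- **Unit of randomisation.** Sequence generation {16a} states "Each clinical site is a cluster", and Implementation {16c} states "Individual clinics will be assigned to the intervention and TAU on a 5:1 ratio". Participants take the arm of the clinic that treats them. The split is "11 primary care clinics (9 intervention, 2 TAU) and 7 mental health clinics (6 interventions, 1 TAU" clinic, that is, 15 intervention and 3 TAU.
- **Model 1** (Statistical methods {20a}) is an "analysis of covariance with the baseline value (site, racial-ethnic group, number of visits, age, weight, smoking status, and survey scores) as the covariate", comparing values at the end of the study.
- **Model 2** (same section) is a multiple logistic regression with "independent variables such as treatment group and pre-determined baseline covariates (including study site").
- **For both models**, the section adds a term for LACDHS versus LACDMH and its interaction with arm. It says that the cluster design will enter through a suitable variance-covariance structure.
- **Role.** The section describes the covariate-adjusted model as a sensitivity analysis to a simple comparison of cessation, which supplies the primary result.
- **Missing data {20c}.** The last value is carried forward: "if a patient only comes once, their smoking status and other characteristics will be that of baseline measurement".

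**The concern.** There are two separate defects.

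**Site.** When whole clinics are allocated, the intervention effect is a difference between groups of clinics. A model that gives every clinic its own coefficient has already used up all between-clinic information, so nothing is left from which to estimate arm. The planned department term and its interaction with arm are also clinic-level and fail for the same reason. The failure may go unnoticed, because an analyst can still form an arm contrast from the site coefficients, and its default standard error would ignore between-clinic variation.

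**Number of visits.** The covariate is listed as a baseline value. However, the only visits that {20a} counts are study visits: its per-protocol set requires at least three of four, including month 12. That count is complete only at the end of follow-up. Arm may affect it, and the carry-forward rule ties it to the outcome. Adjusting for it replaces the intention-to-treat contrast with one conditional on post-randomisation behaviour.

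**Working it through.** **1. The plan's own figure.** Sample size {14} gives 99.4% power for 25% versus 5%, ICC 0.05, two-sided 5%. Take a two-proportion z test with unpooled variance and a design effect of 1 + (m − 1) × 0.05 in each arm, where m is the clinic size, with 14 and 3 clinics. It gives 99.6% for 1000 versus 200 and 98.7% for 500 versus 100 (after 50% dropout), so the stated value lies between the two. A pooled-variance version gives 94.8% and 88.3%. This figure does not depend on the present point.

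**2. Rank of the fixed-effects matrix.** Inputs: 18 clinics, 9 + 6 intervention and 2 + 1 TAU ({16a}).

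| Columns | Number | Rank |
|---|---|---|
| Intercept + 17 site indicators | 18 | 18 |
| The same + arm | 19 | 18 |
| The same + arm, department, arm × department | 21 | 18 |
| Intercept + arm, department, arm × department, without site | 4 | 4 |

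Arm equals the sum of the indicators of the 15 intervention clinics, so it adds no rank. The same holds for any clinic-level variable. {9}, {14} and {16a} give different clinic counts, but with K clinics the rank is K whether or not arm is added. A covariance structure for the residuals does not alter this matrix.

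**3. What a forced contrast would do.** Suppose the averaged site effects of the two arms are compared using within-site error. Assumptions: total variance 1, ICC 0.05 (from {14}), equal clinic sizes m, continuous outcome, no true effect.

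- True variance of a clinic mean: 0.05 + 0.95/m.
- Variance used by the test: 0.95/m.
- Rejection probability: P(|Z| > 1.96/√r), where r is the ratio of the two.

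For m = 33 (600/18, after 50% dropout): 0.0788/0.0288 gives r = 2.74 and √r = 1.654. The effective cut-off is 1.96/1.654 = 1.185, so the test rejects 23.6% of the time. A simulation of 4000 null trials gave 24.35%.

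For m = 67 (1200/18, everyone retained by carry-forward): 0.0642/0.0142 gives r = 4.53 and √r = 2.128. The cut-off is 0.921, so the test rejects 35.7% of the time.

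**4. After removing site.** The four-column model has full rank. For a two-arm, between-clinic t test with 15 + 3 clinics and 50% dropout:

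- Design effect: 1 + (33.3 − 1) × 0.05 = 2.617.
- Effective sizes: 500/2.617 = 191.1 and 100/2.617 = 38.2.
- SE: √(0.05 × 0.95/38.2 + 0.25 × 0.75/191.1) = 0.0472.
- Noncentrality: 0.20/0.0472 = 4.24.

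Power is 98.9% by the normal approximation and 97.8% with t on 16 df.

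**5. Number of visits.** For someone with one visit, the end value equals the baseline value by rule, so the change is exactly zero in either arm. The covariate therefore carries outcome information by construction. If arm influences attendance, its coefficient absorbs or distorts part of the arm effect. The article gives no distribution of dropout times, so neither direction nor size can be calculated.

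**The case against.** - **The primary result is untouched.** This stands. The simple comparison contains neither site nor number of visits, and the repeated-measures analysis names no site covariate. A reader might infer that the trial cannot estimate its intervention effect at all; {20a} does not support that. However, the section promises allowance for clustering only for models 1 and 2, so the models with the defect are the ones meant to respect the design.
- **Site may be meant as a random or clustering factor.** The word fixed does not appear, and the covariance sentence shows that clustering was considered. But a covariate in an analysis of covariance and an independent variable in a logistic regression are fixed effects on their ordinary reading. Site cannot mean department, which is added separately. Leaving coding to an analysis plan does not answer this, because the article itself names site as a covariate.
- **Non-estimability depends on coding.** With site nested in arm, a contrast of averaged site means can be formed. This is correct, and the problem then becomes the error term, as step 3 shows. How the software would handle the redundant arm term was not tested.
- **Number of visits is named only for model 1.** This stands. Nothing shows that it enters the logistic model for cessation.
- **A reader might take the expected 50% dropout to mean that attendance fixes the outcome for half the participants.** That does not follow. A dropout lost after month 3 or 6 carries forward an observed value, which may be abstinence.

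**Conclusion.** The point holds for the covariate-adjusted models. With site entered as clinic indicators, arm, department and their interaction have no degrees of freedom, and this is exact for any number of clinics. If a contrast is forced with within-site error, type I error is about 24% at 33 participants per clinic and about 36% at 67. Those two figures rest on the plan's ICC of 0.05 and on assumed equal clinic sizes and a continuous outcome.

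The listing of number of visits as a baseline covariate in model 1 is also wrong. It can bias the intention-to-treat effect there, by an unknown amount.

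The documents do not support dropping baseline smoking status as constant by eligibility. Entry requires three or more cigarettes or cigars a day, so the amount smoked varies, and the baseline value of the outcome is a proper covariate in an analysis of covariance.

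**What to change.** - Remove site from the covariate lists of models 1 and 2.
- State that clinic is a random intercept, or the cluster in a GEE, with a small-sample correction, because only 3 clinics are TAU.
- Keep LACDHS/LACDMH as a fixed term with its interaction with arm. Note that the interaction will rest on a single LACDMH TAU clinic.
- Delete number of visits from the model 1 covariates and report it only as a description of retention.
- Keep the other true baseline covariates, including the baseline value of the outcome.

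The cost is wording only, with no new data or participants. Intervals for the arm effect will be wider than those based on within-site error, and more honest. Under the plan's own assumptions, using t on 16 df instead of the normal approximation lowers power only from 98.9% to 97.8%.
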